### Postoperative Care

Postoperative care will be similar in both arms and based on enhanced recovery principles, which include early mobilization and expanding oral intake as desired by the patient. Patients will be evaluated for adjuvant chemotherapy at their local oncologic department, according to national guidelines.

#### Treatment of Cancer Recurrence

Treatment of cancer recurrence or progression should follow national guidelines and be decided by a multidisciplinary team. However, local tumor recurrence after ablation will preferably be treated with new ablation, provided approval from the local multidisciplinary team.

In case of new liver metastases, the multidisciplinary team will evaluate the best treatment option for the patient. In cases where resection and ablation are considered equivalent, the treatment following initial randomization should be preferred.

#### Follow-Up

The patient will be contacted by the study center 30 days postoperatively for registration of complications, quality of life, health economy, referral to oncologist, and unblinding.

Routine follow-up will be at 3 months, 6 months, and 12 months postoperatively (Fig. 2). At each of these CT scans of the chest, abdomen, and pelvis; clinical control; and measurement of carcinoembryonic antigen (CEA) will be performed. Quality of life and health economy will be evaluated.

**Fig. 2 Fig2:**
[figure not shown]
New Comet trial flowchart^26^

After completion of follow-up for the primary endpoint (local tumor recurrence), the patients will undergo standard follow-up according to national guidelines. This consists of CT scans of the chest, abdomen, and pelvis; clinical control; and measurement of CEA every 6 months. Additional follow-ups are allowed if clinically indicated, or according to local guidelines provided that planned follow-up is not systematically different between groups.

Any cancer recurrence will be evaluated and verified by an experienced radiologist at the treatment center. A centralized radiology review board will evaluate any suspected local tumor recurrence. Radiologists cannot evaluate a local recurrence following ablations they have performed themselves. In case of unresolved decisions, imaging will be transferred to an external expert center for a final decision.

#### Double Blinding

Patients and medical and nursing staff will be blinded for the type of intervention. At the end of surgery patients will receive a securely taped, 40 cm × 40 cm abdominal dressing to mask their incisions or percutaneous puncture wounds (Fig. 3). This abdominal dressing can be removed when all criteria for functional recovery are met, or at the latest postoperative day 3. Staff will be encouraged not to read digital operation reports until unblinding; but in case of medical need, unblinding by reading digital operation reports is allowed. The surgeon in charge of the patient in the postoperative setting is allowed to unblind themselves for any medical reason. Similarly, all involved healthcare personnel will be unblinded as the patient leaves the hospital (to prepare appropriate discharge reports). The patient will be informed of what treatment they received 30 days postoperatively.

**Fig. 3 Fig3:**
[figure not shown]
Large abdominal dressing ^27^

At Oslo University Hospital double blinding will be performed, while it will not be mandatory in the multicenter setting. It will be up to each center to determine whether blinding is feasible at their institution. However, blinding is encouraged.

#### Data Collection and Monitoring

Baseline characteristics will be recorded before randomization. The required clinical data, i.e., primary and secondary outcomes, will be collected after randomization. All complications will be scored using the Clavien–Dindo score of surgical complications^16^ and the Comprehensive Complication Index.^17^

Follow-up data will be collected from the local hospital or general practitioner by obtaining copies of patient medical records and CT scans. For long-time follow-up data, records will be collected for up to 10 years.

#### Health-Related Quality of Life

Patients will be asked to complete the RAND-36 questionnaire before study intervention and after 1, 3, 6, and 12 months.

#### Cost-Effectiveness

Direct and indirect healthcare costs will be collected in a 12-month perspective after the intervention.

Further details on data collection for health literacy and anesthesiologic substudies can be found in supplementary appendix.

#### Statistical Analysis

The primary outcome of local tumor recurrence within 12 months after study intervention will be analyzed with a Kaplan–Meier plot, a log-rank test for equality of survival curves, and a Cox proportional hazard regression model. The primary analysis will be the Cox regression model, and we will report the estimated hazard ratio (HR) with a 95% confidence interval for thermal ablation versus surgical resection and a p-value for the null hypothesis of no treatment difference (HR 1). The median survival time in each treatment group will be estimated with the Kaplan–Meier estimator and presented with 95% confidence intervals. The outcomes of disease-free and overall survival will be analysed and reported in the same manner as the primary outcome.

Continuous outcomes measured at one time point (i.e. at 12 months) will be analysed with two-sample *t*-test, with adjustments for unequal variances (the Welch *U* test), and 95% confidence interval for the difference between means. In cases where the distribution of the outcome is considerably skewed, median regression will be used and differences in medians instead of means will be analyzed.

Change in continuous outcomes measured at baseline and 12 months will be analyzed with analysis of covariance (ANCOVA), i.e., a linear regression model where the 12 months measurement is the dependent variable and treatment and baseline measurement are the independent variables. The between-treatment difference in change from baseline will be estimated with a 95% confidence interval, and a *p*-value for the null hypothesis of no treatment difference.

Dichotomous variables will be analyzed with Fisher mid-*p* tests and Newcombe hybrid score confidence intervals.^18^ Ordered categorical variables with more than two categories will be analyzed with Wilcoxon–Mann–Whitney tests (score tests for effect in a proportional odds model).^19^ A statistical analysis plan will be prepared and published at clinicaltrials.gov.

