### Endpoints

#### Primary Endpoint

The primary endpoint of the trial is local tumor progression within 12 months. Local tumor recurrence is defined as new tumor tissue adjacent (0 mm distance) to the resection margin or ablation zone at the first imaging where the new tumor is visible.

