### Randomization

Randomization will be electronically performed after all neoadjuvant treatment is administered if applicable, inclusion and exclusion criteria are controlled, and informed patient consent has been obtained. The patients will be allocated to treatment with resection or ablation with an allocation ratio of 1:1. A dedicated electronic randomization software has been created using block randomization with variable block sizes and stratified randomization to ensure similar numbers of the following prognostic factors in both groups:Size of largest tumor over 2 cm.Superficial lesion (no visible liver tissue between tumor and liver surface on preoperative radiology).Treatment center.

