### Sample Size Calculation

Ablation has previously been associated with high local recurrence rate, up to 20%, compared with 2–3% for resection.^13^ Recent analyses of ablation using modern techniques for needle guidance and ablation zone confirmation report local recurrence as low as 4%.^14^

In this trial we expect a local recurrence rate of 2% in the resection group (control) and 7% in the ablation group (intervention). Given that ablation has frequently been used despite expected local recurrence numbers of up to 20%, we consider a non-inferiority margin of 13% acceptable. With a two-sided alpha of 5% and a power of 80%, 208 patients are needed to exclude a difference in favor of the resection group of more than 13 percentage points (equaling a local recurrence percentage of 2% following resection and 15% following ablation). To allow for 10% dropout we aim to include 230 patients in total, 115 in each group.

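### At the planned 2% recurrence rate after resection, the primary Cox model has a 10–12% chance of giving no finite hazard ratio or upper confidence limit

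*Protocol article*

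**What the plan says.** The Statistical Analysis section of the protocol article lists a Kaplan–Meier plot, a log-rank test and a Cox model for local recurrence within 12 months, and gives the Cox model primacy: "The primary analysis will be the Cox regression model, and we will report the estimated hazard ratio (HR) with a 95% confidence interval". The accompanying p-value tests a hazard ratio of 1. The section does not say whether the interval and p-value are of Wald, score or likelihood-ratio type. For dichotomous variables it names Fisher mid-p tests and Newcombe intervals, but it does not assign these to the primary outcome. It announces a separate statistical analysis plan.

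The Sample Size Calculation section works with proportions. It expects 2% local recurrence after resection and 7% after ablation. On the margin it says "we consider a non-inferiority margin of 13% acceptable", meaning 13 percentage points (2% against 15%). It continues: "With a two-sided alpha of 5% and a power of 80%, 208 patients are needed", and "To allow for 10% dropout we aim to include 230 patients in total, 115 in each group". The endpoint is tied to a fixed time under Primary Endpoint: "The primary endpoint of the trial is local tumor progression within 12 months".

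**The concern.** A 2% risk in 104 to 115 patients gives an expected 2.1 to 2.3 events in the control arm, so an arm with no event is a realistic outcome. When every event is in the ablation arm, the Cox partial likelihood keeps rising as the log hazard ratio grows. No finite maximum exists. The upper confidence limit is infinite whether the interval is Wald or unpenalised profile likelihood.

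In a non-inferiority trial the upper limit for ablation against resection is the decisive quantity. Without it, the designated primary analysis cannot support the conclusion the trial is built for, even when the raw counts lie well inside the margin. A substitute would then have to be chosen with the data in view, unless a rule had been fixed beforehand. The problem is separate from which hazard ratio serves as the null value: replacing 1 by a margin value would leave the estimate and its upper limit infinite.

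**Working it through.** **Inputs.** From Sample Size Calculation: 2% and 7% recurrence, margin 13 points, two-sided alpha 5%, power 80%, 208 evaluable and 230 randomised patients. From Randomization: "allocation ratio of 1:1". So there are 104 evaluable or 115 randomised patients per arm.

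**1. The plan's own figure.** With unpooled variances,

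n per arm = (1.960 + 0.842)² × (0.02 × 0.98 + 0.07 × 0.93) / (0.13 − 0.05)² = 7.849 × 0.0847 / 0.0064 = 103.9, rounded up to 104.

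The total is 208, as stated. The plan was therefore sized on a risk difference.

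**2. Chance of an empty resection arm,** (1 − p)ⁿ:

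| Resection rate | n = 115 | n = 104 |
|---|---|---|
| 2% (planned) | 0.98^115 = 9.8% | 0.98^104 = 12.2% |
| 3% | 3.0% | 4.2% |
| 4% | 0.9% | 1.4% |
| 14% | practically 0 | practically 0 |

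The Sample Size Calculation section cites 2–3% for resection. The 4% and 14% figures are those cited in the introduction for earlier studies and for the COLLISION trial. At 7%, the chance that the ablation arm is also empty is below 0.1%, so it can be ignored.

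**3. What the Cox model then returns.** Data sets were constructed with no resection event, distinct event times and no early censoring. The log hazard ratio ran to about 20, where the iterations stopped on the convergence tolerance.

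| Recurrences, resection v ablation | Wald p | Score p | Likelihood-ratio p | Unpenalised profile limits for the HR |
|---|---|---|---|---|
| 0/104 v 4/104 | 0.999 | 0.044 | 0.018 | 1.65 to infinity |
| 0/104 v 7/104 | 0.998 | 0.007 | 0.0016 | 3.3 to infinity |
| 0/115 v 8/115 | 0.998 | 0.004 | 0.0008 | 3.8 to infinity |

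The score test here is the log-rank test that the article also lists. The Wald p-value alone breaks down; the missing upper limit is common to both unpenalised interval methods.

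**4. The same kind of data on the risk-difference scale** (Newcombe 95% interval, ablation minus resection):

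- 0/115 v 5/115: 4.3 points (0.3 to 9.8), inside the 13-point margin.
- 0/115 v 8/115: 7.0 points (2.3 to 13.1), just outside it.
- 0/104 v 7/104: 6.7 points (1.8 to 13.2), just outside it.

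All three give a finite answer that can be set against the margin.

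**5. What a penalised Cox fit would give** (Firth, profile penalised-likelihood 95% interval, 115 per arm):

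- 0 v 5: HR 11.2 (1.3 to about 1470), p = 0.026.
- 0 v 8: HR 17.5 (2.2 to about 2270), p = 0.003.
- 1 v 8: the ordinary HR of about 8.2 becomes 5.8.

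Under proportional hazards, 15% against 2% corresponds to a hazard ratio of ln(0.85)/ln(0.98) = 8.0. The 0 v 5 result, inside the margin as a risk difference, has a Firth upper limit far above 8.0. Penalisation makes the results finite but does not by itself give a usable non-inferiority answer.

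**The case against.** The strongest reply is that the type of test, the interval method and a rule for sparse events belong to the statistical analysis plan, which is announced but not shown. That holds for the test and the interval type, and they are not faulted as omissions here. It does not cover the estimator. The article itself makes the Cox hazard ratio with its 95% interval the primary result, and its own planned event rate makes that result unobtainable in roughly one trial in eight to ten.

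A reader might infer that the primary analysis would report p near 1 whenever the resection arm is empty. The article does not support this, because it names no Wald test. Score and likelihood-ratio tests of the same model give small p-values, and the planned log-rank test and Kaplan–Meier curves would show the difference beside any Wald value.

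A reader might also infer that the model fails exactly when the arms differ most. That is true only of the hazard ratio. At the planned rates, only 29–34% of outcomes with a difference of 10 points or more have an empty resection arm.

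Finally, power lost by a Wald test against a hazard ratio of 1 would be superiority power and says little about a non-inferiority trial. No weight is placed on it.

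**Conclusion.** The point holds in a limited form. At the planned 2% rate there is a 9.8% (115 per arm) to 12.2% (104 per arm) chance that the primary analysis yields neither a finite hazard ratio nor a finite upper limit. These figures assume independent patients with the same 12-month risk and an ordinary unpenalised Cox fit. They are sensitive to the rate: 3–4% if the true rate is 3%, about 1% if it is 4%, and practically nil at the 14% reported for COLLISION. The near-1 p-value is conditional on a Wald test. The infinite upper limit is not. The change should be made, since a failure of this frequency under the sponsor's own assumption can be avoided by wording alone.

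**What to change.** In Statistical Analysis, prespecify for the primary outcome, whatever the event count, the 12-month risk difference with a 95% interval that is valid at zero events, and compare its upper limit with 13 points. The Newcombe interval already named for dichotomous variables would serve. If a hazard ratio is still reported, take it from Firth's penalised Cox model with a profile penalised-likelihood interval, and take the p-value from a score or likelihood-ratio test, not a Wald test.

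This needs no extra patients or data, only a wording change before database lock. Two costs should be stated in the plan. First, a simple difference in proportions needs a rule for patients whose 12-month status is unknown. Second, with few events the Firth hazard ratio is shrunk noticeably towards 1 (about 8.2 to 5.8 at 1 v 8). That favours ablation, and the interval is very wide, so the hazard ratio should not decide non-inferiority alone.

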## Patients and Methods

### Study Design

New Comet is a multicenter randomized controlled trial. The study is powered to determine whether thermal ablation of colorectal liver metastases is non-inferior to resection with regard to local tumor recurrence at 12 months.

This is an ongoing trial at Oslo University Hospital (principal investigator, Oslo, Norway), Karolinska University Hospital (Stockholm, Sweden), University Hospital of North Norway (Tromsø, Norway), and Sahlgrenska University Hospital (Gothenburg, Sweden).

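### As the article states it, the primary analysis (Cox hazard ratio tested against HR 1) does not address the 13-percentage-point non-inferiority margin for which the trial was designed and sized

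*Protocol article*

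**What the plan says.** The Study Design section of the protocol article sets the objective as showing that ablation is "non-inferior to resection with regard to local tumor recurrence at 12 months". The Sample Size Calculation section expects recurrence of 2% after resection and 7% after ablation. It sets the margin at 13 points on the absolute scale (2% against 15%) and concludes: "208 patients are needed to exclude a difference in favor of the resection group of more than 13 percentage points". This uses a two-sided alpha of 5% and 80% power, and 230 patients are enrolled to allow for 10% dropout.

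The Statistical Analysis section then lists a Kaplan–Meier plot, a log-rank test and a Cox model for the primary outcome, and ranks them: "The primary analysis will be the Cox regression model, and we will report the estimated hazard ratio (HR) with a 95% confidence interval". The accompanying test is "a p-value for the null hypothesis of no treatment difference (HR 1"). The section adds: "The median survival time in each treatment group will be estimated with the Kaplan–Meier estimator". It mentions neither the margin nor non-inferiority. Newcombe intervals are named for dichotomous variables in general, while the primary outcome is explicitly assigned to Cox. A statistical analysis plan is announced but not shown.

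**The concern.** The design and the analysis differ in effect measure (absolute risk difference against hazard ratio) and in null hypothesis (at least 13 points worse against no difference). A non-inferiority conclusion needs a confidence limit set against the margin, on the margin's own scale. A p-value against HR 1 cannot supply that. A large one does not show non-inferiority, and a small one does not rule out a true difference below 13 points.

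The question that the trial is powered for would therefore go unanswered by the analysis called primary. With so few expected events, the HR may also be very imprecise or not estimable.

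**Working it through.** **1. The plan's sample size.** Inputs from Sample Size Calculation: 2%, 7%, margin 13 points, one-sided 2.5% (two-sided 5%), power 80%, 1:1 allocation. With the unpooled risk-difference formula:

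n per arm = (1.960 + 0.842)² × (0.02×0.98 + 0.07×0.93) / (0.13 − 0.05)² = 7.849 × 0.0847 / 0.0064 = 103.9, so 104 per arm and 208 in total.

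This matches exactly. Other readings do not: one-sided 5% gives 164, superiority at 2% vs 15% gives 144, and superiority at 2% vs 7% gives 538. So 208 rests on a non-inferiority test of the absolute difference. With 10% dropout, 230 × 0.9 = 207, which is consistent.

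**2. Can the HR interval be read against 13 points?** Under proportional hazards, the HR equal to a 13-point excess at control risk p is ln(1 − p − 0.13) / ln(1 − p).

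| Control risk | HR equal to +13 points |
|---|---|
| 2% (planned) | ln 0.85 / ln 0.98 = 8.04 |
| 3% | ln 0.84 / ln 0.97 = 5.72 |
| 4% | ln 0.83 / ln 0.96 = 4.56 |
| 14% (resection arm of the earlier randomized trial cited in the introduction) | ln 0.73 / ln 0.86 = 2.09 |

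No single HR limit corresponds to the margin.

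**3. Worked outcomes at 104 per arm.** The Newcombe upper limit is d + √[(u_A − p_A)² + (p_R − l_R)²], where u and l are Wilson limits. The Cox results assume evenly spread event times and no censoring before 12 months.

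- 7 ablation vs 2 resection: d = 4.81 points; upper limit = 4.81 + √(6.52² + 1.39²) = 11.5. Margin met. Cox HR about 3.6 (0.74 to 17.2), p about 0.11.
- 14 vs 8: d = 5.77 points; upper limit = 5.77 + √(7.87² + 3.74²) = 14.5. Margin not met. Cox HR about 1.8 (0.76 to 4.29), p about 0.18.
- 6 vs 0: d = 5.77 points; upper limit 12.0. Margin met, but there is no finite HR. The pooled two-proportion score statistic is 0.0577 / √(0.0288 × 0.9712 × 2/104) = 2.49, so a significant difference coexists with non-inferiority.

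**4. Events.** Expected: 104 × 0.02 + 104 × 0.07 = 2.08 + 7.28 = 9.4. The chance of no resection events is 0.98^104 = 12% (0.98^115 = 10%). With 2% to 7% of patients having events, the Kaplan–Meier curve does not approach 50%, so the median will not be reached.

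**5. Would converting the margin to an HR work?** At a 2% control risk the margin is HR 8.04 and the planned truth is ln 0.93 / ln 0.98 = 3.59. SE(log HR) = √(1/2.08 + 1/7.28) = 0.786. Power = Φ(ln(8.04/3.59)/0.786 − 1.96) = Φ(−0.93), about 18%. The plan proposes no such test. The figure only shows why conversion is not a remedy.

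**6. Power of the risk-difference rule (upper 95% limit below 13 points), by exact binomial enumeration.**

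| Interval | Power at 2% vs 7%, 104 / 115 per arm | Type I error at 2% vs 15%, 104 / 115 per arm |
|---|---|---|
| Newcombe | 65% / 71% | 2.1% / 2.3% |
| Unpooled Wald | 78% / 80% | 4.1% / 3.7% |

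Newcombe first reaches 80% at about 139 per arm.

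**The case against.** The strongest reply is that a journal article condenses the protocol, and that the announced analysis plan may contain a margin-based rule. That stands as a limit on the claim. A reader might infer that the trial will never test its margin, or that any non-inferiority conclusion must be post hoc. The article does not support either inference, since a plan finalised before comparative data are seen would be pre-specified. The reply does not remove the point, however. The article is not silent: it names the primary analysis, the effect measure and the null hypothesis, and a margin-based primary analysis would have to override all three.

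A reader might also infer that a non-significant p-value would be taken as non-inferiority. The article states no such rule, so an error rate for it would describe nothing that is planned.

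A 12-month risk difference could be derived from the planned Kaplan–Meier curves, or from the general Newcombe provision, but the article assigns neither to the primary question. A lack of resection events affects the HR but does not prevent the Kaplan–Meier curves or the log-rank test. An unreached median is a harmless descriptive result and carries little weight here.

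**Conclusion.** The point holds for the analysis as this article states it. The stated primary analysis and its null do not address the 13-point absolute margin on which the trial is sized, and no HR interval can be read against that margin without assuming a control risk. Two plausible data sets, both non-significant against HR 1, give upper limits of 11.5 and 14.5 points and so opposite answers. There is about a 12% chance that the named primary estimate is not finite.

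These figures rest on the protocol's 2% and 7%, 104 evaluable patients per arm, and complete 12-month follow-up; the HR conversions also assume proportional hazards. It would be tempting to conclude that the sample size is wrong, but it reproduces exactly under its own formula. The fault lies in the analysis statement and should be corrected before comparative data are examined.

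**What to change.** Before comparative data are seen, define the primary analysis as the difference (ablation minus resection) in 12-month local recurrence risk. It can be estimated from cumulative incidence, Kaplan–Meier or proportions, with stated handling of death and dropout. Give a two-sided 95% confidence interval and declare non-inferiority if its upper limit is below 13 percentage points. Keep Cox and log-rank as supportive analyses, and report 12-month incidence per arm in place of the median.

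Name the interval method and restate its power at the planned size. The Newcombe interval that the plan already uses elsewhere holds the error rate but gives about 65% to 71% power. The Wald interval comes close to the stated 80%, but its type I error is about 4% against the intended 2.5%. A Kaplan–Meier or cumulative-incidence interval would need its own power check.

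The cost is wording in the protocol and analysis plan, plus the possibility that the stated 80% power must be restated lower. No extra data are needed, and no change to enrolment is proposed.

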## Discussion

This trial is designed to assess whether local tumor recurrence following thermal ablation with ablation confirmation software is non-inferior to surgical resection in colorectal liver metastases measuring up to 3 cm.

Local tumor recurrence was chosen as primary endpoint because this has historically been considered the major limitation of thermal ablation. We expect the incidence of local tumor recurrence to decline with introduction of ablation confirmation software. The recently published COVER-ALL study showed that use of software-based assessment during thermal ablation significantly improved the minimal ablative margin compared with visual assessment, and reduced the rate of local tumor recurrence from 15 to 4%.^14^

The New Comet trial has a relatively high non-inferiority margin of 13%. We consider this acceptable as re-ablation of local recurrence is likely to be a minor procedure to these patients. A difference in local tumor recurrence rate is not likely to affect overall survival, and the MAVERRIC trial showed similar survival after resection and ablation despite a rate of 23% local tumor recurrence per patient within 1 year after ablation.^11^ The non-inferiority margin was thoroughly discussed within the study group and with an international group of experts.

Overall survival was not chosen as primary endpoint, as randomized trials are challenging when the expected difference between groups is small. The MAVERRIC trial indicated that microwave ablation has similar overall survival as resection, and these results were validated in the randomized COLLISION trial, although with hazard ratio of 1.30 as upper limit for non-inferiority.

The New Comet trial has several limitations. The trial includes patients who have been previously treated with liver resections and/or ablation. Furthermore, a potential recurrence might be treated with a different modality than the trial randomization. The study centers are Scandinavian with similar healthcare systems. All centers have surgeons experienced in minimal invasive liver surgery and interventional radiologists experienced in percutaneous ablations. The trial will compare ablation and resection in expert hands with advanced technology, and thus limit generalizability to other centers.

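### The Kaplan–Meier median, the only per-arm numerical estimate named for local recurrence within 12 months, cannot be estimated at the expected rates of 2% and 7%

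*Protocol article*

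**What the plan says.** The first paragraph of Statistical Analysis in the protocol article treats the primary outcome as a time to event: "The primary outcome of local tumor recurrence within 12 months after study intervention will be analyzed with a Kaplan–Meier plot", together with a log-rank test and a Cox model. On the comparison between arms it says: "The primary analysis will be the Cox regression model, and we will report the estimated hazard ratio (HR) with a 95% confidence interval". For each arm it then says: "The median survival time in each treatment group will be estimated with the Kaplan–Meier estimator and presented with 95% confidence intervals". 

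The next sentence reads: "The outcomes of disease-free and overall survival will be analysed and reported in the same manner as the primary outcome". That sentence shows that the median is meant for the primary outcome first and is then carried over to the survival outcomes. It cannot be read as a statement about survival only.

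The Sample Size Calculation works with 12-month proportions: "we expect a local recurrence rate of 2% in the resection group (control) and 7% in the ablation group (intervention") and "we consider a non-inferiority margin of 13% acceptable". The Discussion cites an earlier cohort in which survival was similar after the two treatments "despite a rate of 23% local tumor recurrence per patient within 1 year after ablation".

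**The concern.** A median time to recurrence is the time at which half of an arm has recurred. The primary outcome is observed for 12 months and is expected in 2% and 7% of patients, so neither curve comes near 50%. The plan thus fixes a per-arm estimate that the trial cannot produce.

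What is at stake is reporting. The trial was sized on the proportion with local recurrence by 12 months and on a margin in percentage points. If the paragraph is followed as written, the per-arm numerical entry for the primary endpoint will be not reached in both arms. The observed rates could be read off a plot, but the text promises no estimate with an interval to set beside the planned 2%, 7% and 15%.

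**Working it through.** **Inputs.** From Sample Size Calculation: recurrence 2% (resection) and 7% (ablation), margin 13 points (2% against 15%), two-sided alpha 5%, power 80%, 208 evaluable patients, 230 in total, 115 per arm. From Discussion: 23% per patient within one year as the highest one-year rate cited. From Statistical Analysis: Kaplan–Meier median per arm with 95% interval.

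**Step 1. Reproduce the plan's own figure.** For a difference in proportions with unpooled variance,

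n per arm = (1.960 + 0.842)² × (0.02 × 0.98 + 0.07 × 0.93) / (0.13 − 0.05)² = 7.849 × 0.0847 / 0.0064 = 103.9, rounded up to 104, so 208 in total.

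This matches the stated 208. The design therefore rests on 12-month proportions and their difference.

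**Step 2. What a median needs.** Without censoring, half of an arm must recur: 52 of 104, or 58 of 115. Expected events per arm of 115 are 115 × 0.02 = 2.3 and 115 × 0.07 = 8.05.

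**Step 3. Can the curve reach 50% by month 12?** The table uses 104 per arm. The tail probability is binomial, P(X ≥ 52). The lower 95% limit of the curve is (1 − p) − 1.96 × √(p(1 − p)/104). The implied median assumes a constant hazard: 12 × ln 2 / (−ln(1 − p)).

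| 12-month recurrence p | Recurrence-free | Lower 95% limit of curve | P(at least half recur) | Implied median (months) |
|---|---|---|---|---|
| 2% (resection, expected) | 98% | 95% | 2.5 × 10⁻⁵⁹ | 412 |
| 7% (ablation, expected) | 93% | 88% | 3.5 × 10⁻³² | 115 |
| 15% (control rate plus margin) | 85% | 78% | 5.9 × 10⁻¹⁷ | 51 |
| 23% (cited) | 77% | 69% | 1.8 × 10⁻⁹ | 32 |

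The confidence interval fails with the median. Its lower limit is the time at which the lower band of the curve crosses 50%, and in every row that band is still above 50% at month 12.

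**Step 4. Does censoring change this?** Curves were simulated with 115 per arm, exponential times (an assumption), 10% or 30% loss by month 12, and 20,000 runs per setting. None reached 50%. The lowest 12-month values were 0.89 at 2%, 0.80 at 7%, 0.68 at 15% and 0.59 at 23%.

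**Step 5. Does 24 months help?** Under a constant hazard, even 23% per year leaves 0.77² = 0.59, so 59% recurrence-free. The median is still not reached.

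**Step 6. Is the replacement estimable?** Take 104 per arm with 2 and 7 events, ignoring censoring for illustration, and use Wilson intervals:

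- resection 2/104 = 1.9% (0.5% to 6.7%)
- ablation 7/104 = 6.7% (3.3% to 13.2%)
- difference 6.73 − 1.92 = 4.8 points

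The Newcombe limits for the difference are

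- lower: 0.0481 − √[(0.0673 − 0.0330)² + (0.0674 − 0.0192)²] = −0.011
- upper: 0.0481 + √[(0.1325 − 0.0673)² + (0.0192 − 0.0053)²] = 0.115

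so the 95% interval is −1.1 to 11.5 points, which can be read directly against 13 points.

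**The case against.** **The median is only descriptive.** The primary analysis is the Cox model, and no conclusion depends on the median. An entry of not reached is common and biases nothing. This stands, and it is why the severity is modest.

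**The rates will be visible.** A Kaplan–Meier plot is planned and shows each arm's curve to month 12. A reader might infer that the observed rates could not be compared with the planned ones at all. The documents do not support that, because approximate rates can be read from the plot. What is missing from the commitment is a numerical estimate with an interval.

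**The analysis plan may add the estimate.** The article says that a separate plan will be published, and the absence of a 12-month proportion from a condensed article would not be a fault in itself. That stands too. The fault is that the article positively specifies a quantity that cannot be obtained, and an analysis plan that follows it would inherit the problem. The general provision for dichotomous variables (Fisher mid-p, Newcombe intervals) shows that suitable methods are to hand, but the text does not assign them to the primary outcome.

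**Overall and disease-free survival.** Because the median is carried over to these outcomes, a reader might infer that it is equally out of reach there. The documents do not support this. Data Collection and Monitoring provides for records up to 10 years, so a median beyond 5 years could still be observed. The introduction's five-year survival above 55% comes from general surgical reports and is not a projection for this trial. The Discussion also says that most patients operated on for these metastases recur, so a median disease-free survival is plausible.

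**Conclusion.** The point holds for local recurrence. The only numerical per-arm estimate named for the primary outcome cannot be obtained at the expected rates, at the rate implied by the margin, or at the highest one-year rate the article cites. The curves would end at 77% or higher where 50% is needed, and the chance that half of an arm recurs is at most about 2 in a billion across these rates. The conclusion needs only that 12-month recurrence is of the order the article itself gives. The constant hazard and the loss rates enter only the supporting checks.

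The point goes no further than that. It does not show bias in the hazard ratio, an error in the sample size, or a fault in reporting medians for disease-free or overall survival. It is a modest, easily corrected reporting fault.

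**What to change.** In Statistical Analysis, remove the median for local recurrence. State instead that the 12-month cumulative incidence of local recurrence (or the Kaplan–Meier estimate, saying which) will be reported for each arm with a 95% confidence interval, together with the between-arm difference and its 95% confidence interval. Say the same at 24 months for the secondary endpoint. The difference should be included explicitly, because per-arm rates alone cannot be set against the 13-point margin with a stated precision. Keep the median for disease-free and overall survival, to be given where the curve reaches 50%.

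The cost is about one sentence in the article's analysis section, repeated in the analysis plan. It needs no new data, no extra visits or scans, and no change to the sample size or to the Cox model.
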